### Use of ASMs, other therapies and rescue drugs

The type and dosage of all concomitant ASMs are recorded at each protocol-specified visit. Other therapies such as ketogenic diet are also recorded. During the baseline visit, the number of times a rescue drug had been used over the past 12 months is captured, as is rescue drug use between each follow-up visit.

### Healthcare resource utilisation

The number of seizure-related emergency department (ED) visits and seizure-related hospitalisations, as well as the duration of those stays, that have occurred since the previous visit are collected at each visit. At the baseline visit, these outcomes are collected through the previous 12 months. Clinical visits related to VNS programming are also collected.

### VNS Therapy feature use and rationale

Use of optional VNS Therapy features, such as magnet mode, AutoStim, scheduled programming and day/night programming are collected, where applicable, at each visit. In people with Model 1000 (SenTiva) generators, the clinician’s reasons for use of these features are also recorded.

### Safety endpoints

The safety endpoints include all deaths, regardless of cause and relationship to the device or procedure; adverse events related to VNS (including any device deficiencies); and device deficiencies that do not lead to adverse events such as high lead impedance or inaccurate device information.

Adverse events are assessed as ‘possibly’, ‘probably’ or ‘definitely’ related to VNS exclusively by the investigators. Investigators could also specify that they did not know if there was a relationship between the adverse event and the VNS device. No predetermined relationships between adverse events and the treatment were provided to investigators who were expected to make a pragmatic classification of likelihood based on clinical data. All sites were diligently monitored for adverse event reporting and any discrepancy between the clinical record and the study capture forms were highlighted and explanations for this discrepancy documented.

Adverse events are recorded from time of implant until exit from the registry and will be summarised as part of the safety results. All adverse events are also reported to the sponsor’s safety specialists for assessment of their relation to the VNS device for purposes of regulatory reporting requirements. If the registry sponsor and the investigator disagree on the source of an adverse event, both the sponsor’s and investigator’s assessments will be recorded in the database, and the investigator’s assessment will be used for analysis.

### Statistical analysis

Given the exploratory nature of the data set and the principal aim to provide preliminary information on clinical outcome and safety data, the sample size is not calculated based on a statistical power. There are no prospective requirements for enrolment at each centre, meaning that certain centres may contribute a much larger percentage of the study population than others.

Three analysis populations are prospectively defined: modified enrolled population (mENR), modified safety population (mSAF) and the full analysis set (FAS). The mENR or ‘screened’ population are participants with a signed and dated informed consent who meet all registry requirements, consistent with ISO-14155:2011. The mSAF population is defined as all participants in the mENR population who underwent an implantation procedure with the VNS Therapy system, whether that procedure was successful or not. The FAS population includes all participants in the mSAF population with at least one post-baseline efficacy (clinical or performance) assessment. The FAS will be used for efficacy and performance summaries, including all subpopulation analyses. All safety analyses and subject disposition summary will be assessed using the mSAF population.

Further subpopulation analysis will occur in the following groups, provided they include more than 1% of the total subject count:

Age class (paediatric <18 years of age or adult ≥18 years of age).Implant type (new implant or replacement implant).Implant timing (Early: ≤4 ASMs failed or <5 years since initial epilepsy diagnosis at time of implant or Late: All other patients).Seizure type/focus (generalised, focal, combined or unknown).Specific epilepsy syndrome (if known).Epilepsy aetiology (if known).VNS Therapy system model.­ Non-responsive VNS Therapy device: Pulse (Model 102), Pulse Duo (Model 102R), Demi-Pulse (Model 103), Demi-Pulse Duo (Model 104), AspireHC (Model 105).­ AspireSR (Model 106).­ SenTiva (Model 1000).Feature use (AutoStim ON vs OFF; day/night ON vs OFF; scheduled programming ON vs OFF).

Principal analysis of the full cohort data will occur at 3 years of follow-up and will be summarised using descriptive statistics for the relevant analysis population (mSAF or FAS). Intermediate analysis will also be conducted for the full cohort at each year after implant, and topics of this analysis are further described in the following section. Continuous variables will be summarised using the number of observations, mean, median, SD, minimum and maximum values. Categorical variables will be summarised using the number of observations and percentages. Absolute scores and changes from baseline with 95% CIs will be reported for each clinical endpoint at each follow-up visit. VNS-related adverse events, including serious adverse events and deaths, will be presented by system organ class and preferred term as total counts and percentages. These adverse events will be further described by their relationship to VNS implant and/or stimulation and the current status (eg, ongoing, resolved, death, chronic or unknown).

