### Participant eligibility and enrolment

Participants considered eligible for enrolment in CORE-VNS must meet the following criteria:

Clinical diagnosis of DRE to be treated with VNS Therapy. People receiving either initial implants or replacement implants are eligible for enrolment.Able and willing to comply with the frequency of protocol-specified visits.Able to voluntarily provide informed consent, by participant or their legal guardian in accordance with institutional policies. In some cases, individuals who are less than 18 years of age may be required to sign an assent affirming their agreement to participate.

There are no specific exclusion criteria for this all-comers registry. Further, local regulatory approvals may limit access to specific VNS Therapy devices for some patient populations.

Participants are considered enrolled on completion of the baseline visit (which includes affirmation of informed consent) and successful implantation of the VNS Therapy system.

There will be no deviation from standard clinical care and only those people who the clinical team decides are suitable for VNS implantation/replacement will be offered the choice to participate. There will be no change to clinical care based on whether an individual chooses to participate or not. Participants may elect to exit the registry at any time without the need to give a reason and with no adverse impact on their clinical care. Participants who are discontinued by the investigators will have reasons documented for discontinuation (eg, early termination or lost to follow-up). Data from participants who withdraw or are withdrawn from the registry will be included to the point of withdrawal.

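### The safety population inherits an eligibility condition, so a consented, implanted participant found to have failed a registry requirement drops out of the reported safety results

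*Protocol article*

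**What the plan says.** The Statistical analysis section of the protocol article defines three nested populations.

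- **mENR:** "participants with a signed and dated informed consent who meet all registry requirements".
- **mSAF:** "all participants in the mENR population who underwent an implantation procedure with the VNS Therapy system, whether that procedure was successful or not".
- **FAS:** "The FAS population includes all participants in the mSAF population with at least one post-baseline efficacy (clinical or performance) assessment".

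It then assigns the analyses: "All safety analyses and subject disposition summary will be assessed using the mSAF population". Efficacy and performance summaries use the FAS.

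The Safety endpoints section sets a wider scope: "The safety endpoints include all deaths, regardless of cause and relationship to the device or procedure". It adds that adverse events are recorded from implant until the participant leaves the registry and will be summarised with the safety results. It attaches no eligibility condition to either statement.

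The Participant eligibility and enrolment section lists three inclusion criteria: a clinical diagnosis of DRE to be treated with VNS, ability and willingness to keep the visit schedule, and informed consent. It states no exclusion criteria. Data from participants who withdraw or are withdrawn are kept up to that point.

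**The concern.** A safety population normally counts people by exposure. This one nearly does, since it deliberately keeps unsuccessful procedures. But because it is built on mENR, it also requires that all registry requirements be met, so exposure with consent is not enough for entry.

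The registry describes itself as all-comers and long-term safety is one of its aims. A death or device-related event in a consented, implanted person is relevant to that aim whether or not the entry criteria later prove to have been met. On the stated definitions, such an event would be missing from the published safety tables and the person would be missing from the denominator. For common events this would hardly show. For a rare harm, one missing case can change what is reported.

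**Working it through.** The plan states no figure to reproduce: the sample size is not based on power and no breach rate is given. The check is a logical trace, followed by an illustration of scale.

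**Step 1: trace the definitions.** Take a participant who consented, had an implantation procedure, and is later found not to have had DRE.

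1. The DRE criterion is not met, so not all registry requirements are met and the participant is outside mENR.
2. mSAF is a subset of mENR, so the participant is outside mSAF.
3. FAS is a subset of mSAF, so the participant is outside the FAS.
4. All safety analyses use mSAF, so the participant's events are outside the safety results.

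The article names no all-implanted set and no exception for deviations found after implant.

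**Step 2: compare with Safety endpoints.** That section counts all deaths and says recorded adverse events will be summarised. If this participant died, the death would be a safety endpoint under that section but would be excluded under Statistical analysis. Both statements cannot hold for this participant.

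**Step 3: test gentler readings of the requirements clause.** The article does not define the term.

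- If it meant valid consent only, it would repeat the consent condition already in the same sentence.
- If it meant being enrolled, it would require a successful implantation, because that is how the eligibility section defines enrolment. It would then contradict mSAF, which keeps unsuccessful procedures.
- The natural reading left is the entry criteria, which is the reading that creates the problem.

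**Step 4: illustrate the scale.** Inputs: N = 823 enrolled (Study status), used as an approximation to the number implanted. The breach rate b and the per-participant event risk p are assumptions. The number dropped is m = 823 × b, rounded. The chance that at least one dropped participant had an event is 1 − (1 − p)^m.

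| Assumed b | m | p = 1% | p = 2% | p = 5% |
|---|---|---|---|---|
| 0.5% | 4 | 3.9% | 7.8% | 18.5% |
| 1% | 8 | 7.7% | 14.9% | 33.7% |
| 2% | 16 | 14.9% | 27.6% | 56.0% |
| 5% | 41 | 33.8% | 56.3% | 87.8% |

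For example, with b = 1% and p = 2%: 1 − 0.98^8 = 0.149.

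**Step 5: effect on an overall rate.** If the dropped participants have risk r_d and the others r_k, the reported rate is r_k and the rate in everyone implanted is (1 − b) × r_k + b × r_d. The understatement is b × (r_d − r_k). With assumed risks of 10% and 5%, it is 0.01 × 5 = 0.05 percentage points at b = 1%, and 0.05 × 5 = 0.25 points at b = 5% (5.0% reported instead of 5.25%). If the dropped participants carry the same risk as the rest, the rate does not shift at all.

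**The case against.** The strongest reply is that few people can fall into this gap. There are three inclusion criteria and no exclusions. Table 2 places the eligibility check at baseline, and Design limitations says the criteria were judged before any study documentation on a candidate existed. Leaving out people without valid consent is defensible. What remains is essentially a diagnosis overturned after implant. This stands: it makes the number small, and it makes the 5% row above look high. It does not change what the definition does to anyone who is affected.

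Four stronger readings are tempting, and the document does not support them.

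- **Poor attenders are removed after implant.** A reader might infer this from the criterion "Able and willing to comply with the frequency of protocol-specified visits". That criterion is a judgement of ability and willingness at entry. Data are kept up to withdrawal, and the response to visits missed or delayed during the pandemic is a possible subgroup analysis by enrolment year. Withdrawal or missed visits alone remove nobody, so selection on compliance is not shown.
- **The events vanish altogether.** They do not. All adverse events also go to the sponsor's safety specialists for regulatory reporting. The loss is confined to the registry's reported results.
- **The plan hides early losses because disposition starts at mSAF.** Starting disposition at signed consent is a reporting preference. The article refers to a statistical analysis plan, not shown here, which may cover screening counts and the use of mENR.
- **The safety rates are materially biased.** No breach rate or event risk is given, so this cannot be claimed.

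The condensed format is not an answer to the remaining point. The article states these populations as prospectively defined and assigns analyses to them, so this is stated text and not an omission.

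**Conclusion.** The point holds in a limited form. As worded, a consented participant who had an implantation procedure but failed a registry requirement is excluded from mSAF and FAS, and so from the reported safety results. This conflicts with the unconditional scope in Safety endpoints, and the two sections must be reconciled.

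The number affected is unknown and probably small. Under the assumptions shown, an overall event rate would be understated by at most about a quarter of a percentage point, and by less at the more plausible low breach rates. The practical risk is the loss of a single rare event, such as a death. The conclusion rests on reading the undefined requirements as the entry criteria. If the sponsor meant something narrower, a sentence saying so would settle the matter.

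**What to change.** Define mSAF as all participants with informed consent who underwent an implantation procedure, successful or not, regardless of any eligibility deviation. The FAS then inherits the corrected base. Keep the requirement-compliant subset, if it is wanted at all, for a sensitivity analysis only.

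Under this definition the number dropped for an eligibility deviation is zero, and the analysis set matches the scope in Safety endpoints. The cost is one changed definition, and possibly a slightly less favourable reported safety rate. The article already calls for events to be recorded from implant to registry exit, so no new data collection should be needed.

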### Ethics and dissemination

The registry is being conducted in accordance with the ethical principles that have their origin in the Declaration of Helsinki, and that are consistent with Good Clinical Practice described in ISO 14155, and the applicable regulatory requirement(s) of each participating clinical centre. Any additional requirements imposed on the study by a clinical centre’s Institutional Review Board or Ethics Committee will be followed.

Beyond the principal analysis of these results described in the previous section, which will focus on our assessment of the primary clinical and safety outcomes in the FAS and mSAF populations, additional exploratory analyses are expected within this database. The CORE-VNS registry will collect a variety of exploratory clinical outcomes that have not been robustly characterised in a large population treated with VNS. These exploratory analyses will constitute a significant portion of the dissemination strategy for this large database. All results will be submitted to peer-reviewed scientific journals and may also presented as abstracts at large epilepsy congresses with international audiences.

For some of the following analyses, descriptive statistics will be sufficient to describe how practice and outcomes vary, but in other cases direct hypothesis testing is warranted. If hypothesis testing is required for these exploratory analyses, propensity scoring based on baseline demographics and clinical histories will be employed to create matched treatment groups for comparison.

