### Clinical sites

The CORE-VNS registry has currently activated 61 clinical sites across 15 countries (figure 1). The sites and investigators supporting this registry are listed in online supplemental appendix A.

10.1136/bmjno-2021-000218.supp1Supplementary data

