### Regional practice and feature use

This registry aims to better understand regional differences in the implementation of VNS. Specifically, there is interest in identifying regional variances in clinical and safety outcomes associated with different implementations of VNS dosing and standard clinical practice. Newer models of VNS devices have only recently become available in some of the regions participating in the registry, so differences may be apparent in the use of new features. The features available in these newer models offer more programming flexibility and the potential for improved clinical and safety outcomes, but may also add complexity to the therapy. In this study, rationale for the selection of a Model 1000 ‘SenTiva’ generator is collected by ranking the relative importance of each feature in the eventual decision. The rationale options for device or feature selection include: scheduled programming, day/night programming, low heart rate detection, prone position detection, events and trends, availability of AutoStim with a smaller generator.

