### Design limitations

Although VNS Therapy has been approved for the treatment of DRE for nearly 30 years, systematic evaluation of its use in the real-world setting has been lacking. The clinical benefits of the latest advances in model features have not been well studied. Given the prospective design, international recruitment and scale, CORE-VNS is ideally suited to generate the much needed long-term evidence to inform the optimal use of modern VNS.

Nonetheless, the study has several limitations. The primary limitation in the protocol design is that the registry only explores the effects of VNS in those who receive it. There is no direct comparison with a parallel group who do not receive VNS. Therefore, the incremental benefit of adding the therapy to a treatment paradigm can only be assessed by comparing with the participant’s own baseline.

The registry did not enrol all patients with VNS. While all sequential patients were considered for enrolment, the inclusion criteria for the study required that subjects and caregivers be willing and able to comply with the frequency of study visits, and assent/consent to participate. Because the inclusion criteria were assessed before the creation of any study documentation linked to a potential participant, no study documentation exists to assess the risk of bias from non-included patients, which could potentially impact the generalisability of the results. Finally, this registry is observational and was not specifically designed to address any of the exploratory analyses described here with adequate statistical power. It is expected that the large size of this registry will help to reduce the risk of undersampling.

There are practice-specific differences in implementation of VNS. The manufacturer’s recommendations on titration and programming may not be closely followed at all centres, including some centres and practices included in the CORE-VNS registry. There are many legitimate, person-centred reasons for this interpractice variability (eg, tolerability, lifestyle) and there are also fundamental differences in hospital-led and company-led training between regions (including regions within the same country). These differences in therapy implementation may confound regional assessment of clinical and safety outcomes. In all regional analyses, careful attention will be paid to marked variance in VNS settings (as compared with global averages based on this study and historical VNS registry data).

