### Study status

To date, 823 participants have been enrolled in the registry at 61 centres. Enrolment closed by the start of June 2021. Follow-up of participants is expected to continue as planned after termination of enrolment.

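### If regions, or device models and features whose availability varies by region or centre, are formally tested, the stated propensity matching does not account for centre and a participant-level test would reject too often

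*Protocol article*

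**What the plan says.** The rule for testing is in Ethics and dissemination. It is conditional. Some analyses need no test: "For some of the following analyses, descriptive statistics will be sufficient to describe how practice and outcomes vary". Where a test is required, "propensity scoring based on baseline demographics and clinical histories will be employed to create matched treatment groups for comparison". The abstract repeats the idea of matched treatment groups, where sampling allows.

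Regional comparison is a declared aim. Regional practice and feature use speaks of "identifying regional variances in clinical and safety outcomes associated with different implementations of VNS dosing and standard clinical practice" and notes that newer device models came late to some participating regions. The section on healthcare resource utilisation will look at emergency department use by region, and the section on the global safety profile looks to regions where the therapy has been little studied.

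On centres, Statistical analysis warns that "certain centres may contribute a much larger percentage of the study population than others". Design limitations describes differences between practices and in training, even within one country, and concedes that they may confound regional assessment. The remedy it offers is that "careful attention will be paid to marked variance in VNS settings".

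The only mixed model named (Titration guidance and scheduled programming) relates outcomes to programming settings. Its random effects are not listed.

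**The concern.** Region varies only between centres. Matching participants on demographics and clinical history can make them alike in case mix, but it cannot make their centres alike. A participant-level test on the matched set then treats participants as exchangeable across all centres, and any real difference between centres counts as evidence of a difference between regions. The question of interest is whether regions differ by more than centres within a region do.

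The same applies, to a lesser degree, to device model and feature use where these follow what a region or centre has available. There the exposure varies partly within centre, so the variance is understated less, but centre practice can still confound the comparison.

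The article says that exploratory analyses will form a large part of its dissemination. A few large centres with their own practice could produce an apparent regional, model or feature effect with a small p value.

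**Working it through.** The article states no power, ICC, alpha or error rate, so there is no figure of its own to reproduce.

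**Inputs from the article.** Study status: "To date, 823 participants have been enrolled in the registry at 61 centres". Clinical sites: "The CORE-VNS registry has currently activated 61 clinical sites across 15 countries". Hence the mean centre size is m = 823 / 61 = 13.49, and the mean number of centres per country is 61 / 15 = 4.1.

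**Assumed, because not given.** ICC of the outcome within centre (after matching): 0.01 to 0.10. Coefficient of variation (CV) of centre size: 0 to 1. Two-sided level of 5%, taken from the 95% intervals used elsewhere in the article.

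**Formulas**, for an exposure that varies wholly between centres:
- Design effect: DE = 1 + ((1 + CV²) × m − 1) × ICC
- Actual error of a participant-level test: 2 × (1 − Φ(1.96 / √DE))

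**Worked case, ICC 0.05:**
- CV 0: DE = 1 + 12.49 × 0.05 = 1.62, and error = 2 × (1 − Φ(1.96 / √1.62)) = 0.124.
- CV 1: DE = 1 + (2 × 13.49 − 1) × 0.05 = 2.30, and error = 2 × (1 − Φ(1.96 / √2.30)) = 0.196.

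**Full range, all participants retained** (error, and multiple of 0.05):

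| ICC | CV 0 | CV 0.8 | CV 1 |
|---|---|---|---|
| 0.01 | 0.065 (1.3) | 0.075 (1.5) | 0.081 (1.6) |
| 0.02 | 0.080 (1.6) | 0.100 (2.0) | 0.112 (2.2) |
| 0.05 | 0.124 (2.5) | 0.172 (3.4) | 0.196 (3.9) |
| 0.10 | 0.191 (3.8) | 0.267 (5.3) | 0.301 (6.0) |

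**If matching keeps half of each centre** (m halved):

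| ICC | CV 0 | CV 0.8 | CV 1 |
|---|---|---|---|
| 0.01 | 0.057 (1.1) | 0.062 (1.2) | 0.065 (1.3) |
| 0.02 | 0.063 (1.3) | 0.074 (1.5) | 0.080 (1.6) |
| 0.05 | 0.084 (1.7) | 0.110 (2.2) | 0.124 (2.5) |
| 0.10 | 0.118 (2.4) | 0.166 (3.3) | 0.191 (3.8) |

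The lower end of the overall range, 1.1, therefore already includes loss to matching.

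**Check by simulation.** Two regions of 30 and 31 centres, no true regional difference, equal numbers of participants drawn from each, 1,500 runs per setting. The participant-level t-test rejected as follows at ICC 0.02, 0.05 and 0.10:
- CV 0: 0.067, 0.109, 0.190
- CV 0.8: 0.096, 0.168, 0.255
- CV 1: 0.101, 0.159, 0.277

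These are close to the formula, mostly a little lower. With 15 against 46 centres and CV 0.8 the rates were 0.088, 0.142 and 0.209.

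**Does using centre as the unit repair it?** In the same runs a t-test on centre means rejected in 0.035 to 0.059 of runs with 30 against 31 centres (ICC 0 to 0.10), which is about nominal. With 15 against 46 centres it rejected in 0.017 to 0.029, which is conservative.

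**The case against.** The strongest reply is that the article does not state the analysis being criticised. Testing is conditional, description is allowed, the matching is of treatment groups, and a region is not a treatment. Region is not in the list of subpopulations, and none of the regional sections names a test. A reader might infer that regional comparisons are going to be tested on matched participants. The text does not support that, so the point can be made only for the case that they are.

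A reader might also infer that centre has been excluded. It has not. The article describes how groups are formed and is silent on the outcome model and standard errors after matching. It refers to a statistical analysis plan that is not shown, and variance estimation often belongs there. This stands as a limit on the point but does not remove it. The article chose to name its technique for testing, and that technique addresses differences between participants. It also named centre practice as a threat to regional conclusions, and paired that threat with a safeguard that is not a variance term and covers settings alone.

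The size is open to challenge too. The simulation drew participants at random and had no propensity step. Matching may remove centre variation due to measured case mix and may shrink centres. Both lower the inflation, and the second table shows the effect of the latter.

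Finally, one could extend the point to the descriptive intervals in Statistical analysis: "Absolute scores and changes from baseline with 95% CIs will be reported for each clinical endpoint at each follow-up visit". That does not follow. They summarise the cohort, the article does not say how they are computed, and inference to a wider population of centres would be the reviewer's choice of target.

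**Conclusion.** The point holds in conditional form. If regions are formally tested by the stated technique and at participant level, the test will be anti-conservative whenever centres differ. If device models or features that follow regional or centre availability are tested that way, the comparison can be confounded by centre. The article's own account of unequal centres and differing practice makes both likely enough to plan for.

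The size is an assumed range. For regional tests it is 1.3 to 6.0 times the nominal 5% with all participants retained, and 1.1 to 3.8 times if matching keeps half of each centre. Sixfold needs ICC 0.10 and CV 1 together. With all participants retained, the error stays below twofold at ICC 0.01, and at ICC 0.02 with equal centres. A reader might take a fixed inflation of two to six times as established, but the documents give no ICC, centre-size variation or alpha to support it. For device models and features that vary partly within centre, these figures are too high as a measure of variance inflation, and they say nothing about the size of any confounding.

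**What to change.** In Ethics and dissemination, and again in Regional practice and feature use, state that any formal test of region, or of a device model or feature whose availability varies by region or centre, accounts for centre after the propensity adjustment. Either a random intercept for centre or cluster-robust standard errors with a small-sample correction will do. State also that a region with only a few centres is reported descriptively without a p value, with the threshold fixed in advance. At about four centres per country, this would probably cover many single-country comparisons.

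The descriptive full-cohort intervals need no change on this account.

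The change is to analysis wording and uses data already held. Its price is wider intervals and fewer significant regional differences. A simple test on centre means can be conservative when the numbers of centres are very unequal, as the run with 15 against 46 centres shows.
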